## Abstract

**Background:**

Vitamin D does not only regulate calcium homeostasis but also plays an important role as an immune modulator. It influences the immune system through the induction of immune shifts and regulatory cells resulting in immunologic tolerance. As such, vitamin D is thought to exert beneficial effects within the transplant setting, especially in kidney transplant recipients, considering the high prevalence of vitamin D deficiency in kidney transplant recipients.

**Methods/Design:**

The VITA-D study, a randomized, placebo-controlled, double-blind study with two parallel groups including a total of 200 kidney transplant recipients, is designed to investigate the immunomodulatory and renoprotective effects of cholecalciferol (vitamin D_3_) within the transplant setting. Kidney transplant recipients found to have vitamin D deficiency defined as 25-hydroxyvitamin D_3 _< 50 nmol per liter will be randomly assigned to receive either oral cholecalciferol therapy or placebo and will be followed for one year. Cholecalciferol will be administered at a dose of 6800 International Units daily over a time period of one year.

The objective is to evaluate the influence of vitamin D_3 _substitution in vitamin D deficient kidney transplant recipients on the post-transplant outcome. As a primary endpoint glomerular filtration rate calculated with the MDRD formula (modification of diet in renal disease) one year after kidney transplantation will be evaluated. Incidence of acute rejection episodes, and the number and severity of infections (analyzed by means of C-reactive protein) within the first year after transplantation will be monitored as well. As a secondary endpoint the influence of vitamin D_3 _on bone mineral density within the first year post-transplant will be assessed. Three DXA analyses will be performed, one within the first four weeks post-transplant, one five months and one twelve months after kidney transplantation.

**Trial Registration:**

ClinicalTrials.gov NCT00752401

## Background

### Vitamin D and vitamin D deficiency

Vitamin D is a steroid hormone important for the regulation of calcium homeostasis and bone metabolism. There are two ways of obtaining vitamin D, either from the diet or by cutaneous production. Exposure of the skin to ultraviolet light induces the conversion of 7-dehydrocholesterol to previtamin D_3 _which then spontaneously isomerizes to vitamin D_3 _(cholecalciferol). Two hydroxylation steps in the metabolic activation of vitamin D_3 _are necessary to convert it into its physiologically active form 1,25-dihydroxyvitamin D_3 _[calcitriol; 1,25(OH)_2_D_3_]. Vitamin D_3 _is first hydroxylated in the liver to 25-hydroxyvitamin D_3 _[calcidiol, 25(OH)D_3_] and subsequently converted to 1,25-dihydroxyvitamin D_3 _by 1α-hydroxylase in the kidney [1].

25-hydroxyvitamin D_3 _is considered the most reliable indicator of vitamin D status as it reflects an individual's dietary intake of vitamin D on the one hand and the endogenous production in the skin on the other hand [2]. However, endogenous synthesis of vitamin D_3 _is more important to achieve adequate body stores than dietary intake due to the fact that vitamin D is found in a limited variety of foods, mainly oily fish. Casual exposure to sunlight supplies about 90% of the vitamin D requirement for most people [3].

Especially, the elderly and chronically ill are at high risk to develop vitamin D deficiency due to poor dietary vitamin D intake on the one hand and their often modest outdoor activities and the lack of exposure to sunlight on the other hand [4,5]. Moreover, the capacity of human skin to produce vitamin D_3 _decreases in elderly subjects compared to younger adults [3]. In a hospital setting, Thomas et al. reported 57% of hospitalized patients to be vitamin D deficient defined as 25-hydroxyvitamin D_3 _≤ 37 nmol per liter [4].

Accordingly, a high prevalence of vitamin D deficiency was found in predialysis patients with moderate and severe chronic kidney disease as well as in patients undergoing hemodialysis [6,7]. Analyses of pretransplant 25-hydroxyvitamin D_3 _levels showed that only about 15% of kidney transplant recipients have adequate vitamin D levels at the time of transplantation [8,9]. After kidney transplantation vitamin D deficiency remains a common problem as kidney transplant recipients are advised to avoid direct sun exposure because of the high risk of skin cancer due to immunosuppressive therapy [10]. Considering the fact that also dietary calcium and vitamin D intakes are often inadequate in kidney transplant recipients [11] they are at especially high risk to develop vitamin D deficiency. Querings et al. analyzed serum 25-hydroxyvitamin D_3 _levels in 31 kidney transplant recipients who all protected themselves from sun exposure compared with an age- and gender-matched control group at the end of winter. Serum 25-hydroxyvitamin D_3 _levels were significantly lower in kidney transplant recipients compared with controls, with 10 out of 31 having undetectable serum 25-hydroxyvitamin D_3 _levels [12]. For long term kidney transplant recipients Stavroulopoulos et al. reported vitamin D insufficiency (40–75 nmol per liter) to be present in 43%, deficiency (12–39 nmol per liter) in 46% and severe deficiency (< 12 nmol per liter) in 5% [13].

### Substitution of vitamin D deficiency

Considering the high prevalence of vitamin D deficiency in kidney transplant recipients the investigation of vitamin D substitution is of particular interest and relevance to renal transplant patients.

Chronic kidney disease is accompanied by decreased production of the active form of vitamin D, 1,25-dihydroxyvitamin D_3_, due to a reduction in renal parenchyma leading to decreased 1α-hydroxylase available for converting 25-hydroxyvitamin D_3_. Therefore, active vitamin D supplements have effectively been used in order to maintain calcium homeostasis and to decrease the risk of hyperparathyroidism in patients with chronic kidney disease.

However, it is still important to correct calcidiol deficiency as 25-hydroxyvitamin D_3 _serves as a substrate for 1α-hydroxylase not only in the kidney but also in several extra renal tissues. For instance, there is evidence that immune cells express 1α-hydroxylase and are therefore able to synthesize active vitamin D locally. Thus, these tissues are dependent on adequate 25-hydroxyvitamin D_3 _substrate for adequate local 1,25-dihydroxyvitamin D_3 _production [14].

As such, vitamin D is thought to be a potent immune modulator.

### Immunomodulatory properties of vitamin D

Besides its classical actions in calcium homeostasis and bone metabolism vitamin D plays an important role in the immune system [15,16]. Due to its potential to modulate the immune response vitamin D is thought to have beneficial effects within the transplant setting. Calcitriol was shown to improve graft function and graft survival in different models of transplantation and it is also assumed to lead to less acute rejection episodes [17]. Data relating infections to vitamin D status are sparse. There is some evidence that low 25-hydroxyvitamin D_3_levels are associated with an increased risk of infections [18,19].

Calcitriol acts as an inhibitor of the adaptive immune system with T-lymphocytes and antigen-presenting cells as key targets [20]. On the one hand 1,25-dihydroxyvitamin D_3 _is able to shift the T-cell response towards a T-helper 2 phenotype which is considered to be protective in transplantation [21] and on the other hand it induces dendritic cells with tolerogenic properties resulting in T-cell hyporesponsiveness. This means that dendritic cells modulated by 1,25-dihydroxyvitamin D_3 _are able to inhibit T-cell proliferation and their cytokine production (e.g. Interferon-γ), thus, inducing regulatory T-cells with suppressive activity rather than effector T-cells [22,23]. These effects are not limited to in vitro experiments, but could also be demonstrated in models of allograft rejection [24,25].

In clinical trials, a beneficial impact of calcitriol administration in kidney transplant recipients on graft function, overall graft survival and incidence of acute rejection episodes was demonstrated [26-29]. However, these studies are retrospective studies that do not provide definitive evidence of the assumed beneficial immunological effects. In a small prospective study Ardalan et al. investigated the effect of calcitriol started in the donor six days before donation and continued in recipient side for six months after transplantation. Expansion of CD4+ CD25+ regulatory T-cells was observed in the recipients [30] providing strong evidence for the immunomodulatory properties of active vitamin D in kidney transplant recipients.

### Renoprotective properties of vitamin D

In several studies beneficial effects of active vitamin D on progression of chronic kidney disease were documented, either by interfering with the transforming growth factor beta 1 (TGF-β1) signaling pathways or with the renin-angiotensin-aldosterone system, both considered to be important modulators of the progression of renal insufficiency [31,32].

1,25-dihydroxyvitamin D_3 _was shown to function as a negative regulator of the renin-angiotensin system in animals [33]. Recently, Freundlich et al. demonstrated that paricalcitol, a calcitriol analog, leads to a reduction in mRNA levels and protein expression of angiotensinogen, renin, and renin receptor in the 5/6 nephrectomized rat model of kidney disease resulting in less glomerular and tubulointerstitial damage, hypertension and proteinuria [34].

In diverse rat models of kidney disease 1,25-dihydroxyvitamin D_3 _was reported to attenuate the development of glomerulosclerosis and progression of albuminuria accompanied by a lower expression of TGF-β1 in the kidney [35,36].

Furthermore, the podocyte was identified as an important target for the action of 1,25-dihydroxyvitamin D_3_. Calcitriol reduces podocyte loss and changes of podocyte foot process structure leading to a decreased albumin excretion [37,38].

A recent clinical trial indicated that paricalcitol reduces proteinuria in patients with chronic kidney disease. Agarwal et al. analyzed the effect of paricalcitol on proteinuria in 195 chronic kidney disease patients stage 3 and 4 compared to placebo. After six months 51% of the paricalcitol treated subjects compared to 25% of the placebo treated subjects were found to have a reduction in proteinuria independent from the use of inhibitors of the renin-angiotensin-aldosterone system [39].

TGF-β1 is furthermore considered to play an important role in the development of chronic allograft nephropathy. Chronic allograft nephropathy is characterized by interstitial fibrosis and glomerulosclerosis and frequently leads to late allograft loss in kidney transplantation [40]. There is evidence that calcitriol interferes with TGF-β1 mediated gene and protein expression and therefore influences the effects of TGF-β1 in chronic allograft nephropathy [41]. Hullett et al. investigated the efficacy of active vitamin D as monotherapy to prolong allograft survival and preserve renal function in a rat model of chronic allograft nephropathy. 1,25-dihydroxyvitamin D_3 _not only was reported to prolong graft survival but also to prevent histological changes typically found in chronic allograft nephropathy by altering TGF-β1 and matrix regulating molecules [42]. In clinical studies, patients with chronic allograft nephropathy were significantly linked with persistently higher plasma TGF-β1 levels [43].

1,25-dihydroxyvitamin D_3 _obviously has an impact on innate and adaptive immunity, both responsible for acute rejection and chronic allograft nephropathy which is often observed to start only a few months after kidney transplantation.

## Methods

### Objectives

The proposed study is designed to evaluate whether cholecalciferol substitution in vitamin D deficient kidney transplant recipients has beneficial effects upon the post-transplant outcome compared to placebo. As a primary outcome we will evaluate the impact of cholecalciferol on

- graft function (analyzed using glomerular filtration rate calculated with the MDRD formula as well as albuminuria) one year after kidney transplantation

- the incidence of acute rejection episodes within the first year after kidney transplantation, and

- the frequency and severity (analyzed by means of C-reactive protein levels) of infections within the first year after kidney transplantation.

As a secondary objective we will assess whether cholecalciferol substitution influences the common decline of bone mineral density within the first year after kidney transplantation [44] analyzed by means of absolute bone mineral density (g/cm^2^).

Moreover, courses of calcium levels will be observed in order to assess the safety of cholecalciferol administration at 6800 International Units (IU).

### Study design and setting

The VITA-D study is a single-center, randomized, placebo-controlled parallel group study with blinding of patients, study staff, and outcome assessors. Patient recruitment, kidney transplants, postoperative care, and follow-up are conducted at the Medical University of Vienna. The study is planned to start in January 2009. There are about 150 kidney transplants performed annually at the Medical University of Vienna. Approximately 30% of all kidney transplant recipients are expected to be vitamin D deficient defined as 25-hydroxyvitamin D_3 _< 50 nmol per liter. In case there are less than 60 subjects included in the trial after one year it is intended to recruit two other transplant centers.

### Study population and sample size

The study sample will consist of 200 kidney transplant recipients found to be vitamin D deficient (25-hydroxyvitamin D_3 _< 50 nmol per liter) with 100 subjects in each study group. Inclusion and exclusion criteria are detailed in the Appendix. The recruitment phase will last approximately four years with a follow-up period of one year for each subject. A flowchart of the VITA-D study is shown in Figure 1. The sample size calculation was performed according to the following assumptions: Based on the Vienna General Hospital database we concluded that the mean serum creatinine level one year after transplantation is x_1 _= 1,9 mg per deciliter with sigma, the common standard deviation, estimated to be σ = 0.5. An expert panel evaluated that a difference in serum creatinine levels of 0,2 mg per deciliter would represent a significant clinical improvement for the patient. Assuming that α = 0.05 and the power = 0.80 a sample size of 99 for each sample was calculated.

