### Statistical analysis

Baseline data will be expressed as mean values ± standard deviation for symmetrically distributed continuous variables, as median and 25th and 75th percentiles for asymmetrically distributed continuous variables, and as absolute and relative frequency for categorical variables.

Serum creatinine values after one year (the primary endpoint) will be compared between the groups by analysis of covariance (ANCOVA), taking into account as covariates creatinine value at randomization, 25-hydroxyvitamin D_3 _at baseline, and variables which, despite randomization, exhibit large group differences at baseline. ANCOVA will also be applied to the area under the curve of repeated measurements on serum creatinine, CRP, and bone mineral density during the first year of follow-up, using the same set of covariates. Categorical variables (number of acute rejection episodes and infections within the first year after transplantation) will be analyzed using χ^2^-test or fisher's exact test, as appropriate.

All analyses will be performed using an "efficacy subset analysis". Patients are included in this analysis if the study medication has been administered for more than seven days.

Moreover, courses of calcium levels will be described. Furthermore, the Bonferroni-Holm correction will be performed to preserve the global significance level of 5%.

Statistical analysis will be performed with SPSS.

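### The 80% power belongs to one unadjusted 5% test of creatinine, but the analysis section applies Bonferroni-Holm without exempting that endpoint, so the two do not match

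*Protocol article*

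**What the plan says.** All references are to the protocol article.

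- **Study population and sample size.** The target is "a difference in serum creatinine levels of 0,2 mg per deciliter would represent a significant clinical improvement for the patient", with "the common standard deviation, estimated to be σ = 0.5". The result: "Assuming that α = 0.05 and the power = 0.80 a sample size of 99 for each sample was calculated". The plan enrols 200 patients, "with 100 subjects in each study group". No multiplicity allowance and no loss rate are given.
- **Statistical analysis.** One-year serum creatinine is labelled the primary endpoint and compared by ANCOVA, with creatinine at randomization among the covariates. Five further comparisons follow: areas under the curve for creatinine, CRP and bone mineral density, plus acute rejection and infections. Then: "Furthermore, the Bonferroni-Holm correction will be performed to preserve the global significance level of 5"%. The members of the family are not listed and no endpoint is exempted. On the analysis set: "Patients are included in this analysis if the study medication has been administered for more than seven days".
- **Objectives.** "As a primary outcome we will evaluate the impact of cholecalciferol on" introduces three bullets: graft function (MDRD GFR and albuminuria), acute rejection, and frequency and severity of infections.
- **Abstract.** One primary endpoint, MDRD GFR at one year, with rejection and infections monitored alongside it.

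**The concern.** A global 5% level shared over several outcomes and a full 5% level for creatinine can both hold only if the tests are ordered or creatinine is placed outside the correction. The article does neither. The test that was sized is therefore not clearly the test that will be run.

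Two things are at stake. If creatinine shares the 5%, a true difference of 0.2 mg/dl could be missed more often than the stated 20%, and a negative result would be read with too much confidence. And if the family is settled only after the data are seen, that choice could decide whether the trial is positive. Separately, a margin of one patient per arm leaves almost no room for missing one-year values.

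**Working it through.** **Inputs.** From the sample-size section: difference 0.2 mg/dl, SD 0.5 mg/dl, α = 0.05, power 0.80, 100 per arm planned. Assumed, because the article does not state them: family size m, loss of 0% or 10%, baseline-to-one-year correlation ρ of 0, 0.3 or 0.5.

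**1. Reproduce the plan's figure.** n per arm = 2(1.960 + 0.842)² × (0.5/0.2)² = 98.1, rounded up to 99. A one-sided test would give 78, so the stated 99 implies a two-sided test. At 100 per arm the t-test has 80.4% power. The 80% therefore belongs to one unadjusted two-sided 5% test.

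**2. Possible family sizes.** Three if each bullet in Objectives is one hypothesis. Five if each measure in those bullets counts (GFR, albuminuria, rejection, infection frequency, infection severity). Six if the comparisons in the Statistical analysis section are counted. The article endorses none of these.

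**3. Power for creatinine at the first Holm step.** The level is 0.05/m and the noncentrality is 0.2/(0.5 × √(2/n)), which is 2.83 at n = 100 and 2.68 at n = 90. Two-sided t-test, no covariate gain:

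| Tests m | Level | 100 per arm | 90 per arm (10% loss, assumed) |
|---|---|---|---|
| 1 | 0.05 | 80.4% | 76.1% |
| 3 | 0.0167 | 66.1% | 60.6% |
| 5 | 0.01 | 59.1% | 53.3% |
| 6 | 0.0083 | 56.6% | 50.7% |

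**4. Later Holm steps.** Creatinine faces 0.05/m only if no other outcome has already been rejected. In a simulation with three independent endpoints and 100 per arm (normal approximation, unadjusted power 80.7%), power for creatinine was 67% if the other two have no effect, 76% if each has about 80% unadjusted power, and 80% if their effects are very strong. The step 3 values for m > 1 are thus floors for the given m, n and ρ.

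**5. Covariate gain.** Adjusting for baseline creatinine multiplies the residual SD by √(1 − ρ²): 0.954 at ρ = 0.3 and 0.866 at ρ = 0.5. First-step power:

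| Case | ρ = 0.3 | ρ = 0.5 |
|---|---|---|
| m = 3, 100 per arm | 70.9% | 80.2% |
| m = 6, 100 per arm | 61.8% | 72.5% |
| m = 3, 90 per arm | 65.4% | 75.2% |

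**6. If Holm does not cover the primary.** Only loss matters: 80.4% at 100 per arm, 76.1% at 90 per arm, and 79.9% at 90 per arm with ρ = 0.3.

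**The case against.** The strongest reply is that the article names a single primary endpoint, both in Statistical analysis and, in the singular, in the Abstract. Holm can then be read as covering only the other tests, and little power is lost. That reading is tenable, but the text does not state it, and Objectives lists three primary groups. The point therefore stands as a conflict to be resolved, with a power loss that depends on how it is resolved.

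Other objections hold in part:

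- A reader might infer that the design delivers 57–66% power. The documents do not support this as a fact. The range is the first-step floor for six to three tests, with no loss and no baseline adjustment. The larger families are also open to question: five counts albuminuria, for which no test is named, and six counts bone mineral density, which Objectives calls secondary.
- A reader might infer that a true effect would be missed twice as often as stated. With three tests the first-step miss rate is 34% against 20%, about 1.7 times. A doubling needs five or six tests.
- A reader might call the sample-size arithmetic wrong. It is right; it answers a different question from the analysis.
- The 10% loss is an assumption. The analysis set drops only patients with seven days or less of medication, blood is drawn at regular visits through the year, and handling of missing values may sit in a document not shown.

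On covariate gain, the sample-size section claims none and no correlation is given. Randomization is on day five after transplantation, so a strong correlation between that creatinine and the one-year value should not be presumed.

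**Conclusion.** The point holds as a mismatch between the sample-size and analysis sections. If creatinine is inside the Holm family, its power at 100 per arm could be as low as about 66% (three tests) or 57% (six tests) before any covariate gain. Later Holm steps and ANCOVA could restore some or all of this: with three tests, a correlation of 0.5 is enough to reach 80%, and a correlation of 0.3 gives 71%. If creatinine is outside the family, the only shortfall comes from attrition, at 76% for a 10% loss and about 80% with a correlation of 0.3. Family size, loss rate and correlation are all assumptions, so no single delivered power can be claimed. What is certain is that the stated 80% applies to one unadjusted test with 99 of 100 patients per arm evaluable, and that the article does not commit to that test.

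**What to change.** 1. **Statistical analysis:** state that the single primary endpoint is tested first at the full two-sided 5%, and that Bonferroni-Holm applies only to the remaining listed outcomes, once the primary is significant. List those outcomes.
2. **Abstract and Objectives:** name the same one primary measure, either serum creatinine or MDRD GFR, and move rejection and infection to secondary. If GFR is chosen, the sample-size inputs have to be given on that scale.
3. **Sample size:** restate power for the expected evaluable number, with the loss rate and any covariate gain labelled as assumptions; for example, 76% at 90 per arm before covariate gain.

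These changes should be fixed before unblinding. They are changes of text and need no increase in enrolment. The cost is that rejection and infection can no longer succeed on their own, and that the stated power becomes slightly less favourable. Keeping several co-primary outcomes under Holm would be the dearer course: with five tests, 80% power at the first step would take 148 per arm before any covariate gain.
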